### Pilot-testing interventions

Before the trial we will test the feasibility of the intervention strategies and research design using qualitative and quantitative methods. Specifically, we will explore the feasibility and acceptability of the intervention strategies from the perspective of the hospital management staff and family physicians, village doctors and patients/caregivers. We will also explore the feasibility of the study design process, including recruiting family physicians and recording the number of eligible outpatient visits.

#### Key activities

We will purposively select two township hospitals, with one township hospital randomly allocated to the intervention treatment and the other allocated to the control arm. We will also invite private village doctors associated with the intervention site for the initial training. We will test all interventions and study processes in one township hospital, while observing what the usual care is in another. We follow the same informed consent process as outlined in the trial.

#### Pilot evaluation

The pilot study will run for 3 months. For the pilot evaluation we will employ a mixed-methods approach and collect data using in-depth interviews with family physicians in township hospitals and patients, as well as a questionnaire administered to all family physicians after training. The questionnaire methodology is very similar to that used in our process evaluation (see the ‘Process evaluation’ section). The pilot evaluation is guided by the MRC framework for process evaluations [31]. A planning matrix, adapted from our previous trial in Guangxi, can be found in Additional file 1 that illustrates our objectives, intended topics, information required, sources of information and methods for data collection. In the intervention cluster we will conduct in-depth interviews with two family physicians, two village doctors and one township hospital director, and we will conduct one focus group discussion with patients or their caregivers. We plan to do five in-depth interviews with family physicians and one focus group discussion with two to three patients or their caregivers during the pilot study. We will administer the questionnaire to family physicians before and near the end of the pilot study period. We will also perform structured observations to record training and implementation (e.g. consultations) processes during the pilot period.

Our qualitative methods adopt an interpretive description approach and we will employ thematic analysis as described by Braun and Clarke [32, 33]. We will analyse qualitative data as soon as possible after it has been collected. This approach allows for reflexive identification of themes from interviews and observations which can feed into subsequent interviews. For example, if interesting issues emerge they can be followed up in further interviews. As this is a mixed-methods pilot evaluation, our qualitative results will be analysed with our quantitative questionnaire results to provide feasibility and acceptability on both the intervention and control clusters, as well as on feasibility of meeting the sample size (of the prescriptions).

At the end of the pilot study period we will decide whether to continue with the full trial based on the analysis of the planning matrix. The key criteria would be based on: (1) having sufficient levels of recruitment to likely meet the required number of prescriptions for the trial, and (2) the intervention implementation is judged to be feasible: specifically, it must appear feasible to train at least 60% of family physicians; 80% of family physicians who are trained employ the intervention guidelines at the end of the pilot evaluation period.

### Outcomes

We will collect all outcomes and variables from EMR data on all prescriptions issued to eligible outpatients attending trial township hospitals during the 12 months before randomisation (the ‘baseline’ period) and the 12-month trial period. We define all outcomes at the cluster level and will calculate them from the individual-level prescription data for analysis as single summary outcome values (proportions/means) per cluster.

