Provider side	1. Improved antibiotic stewardship programme: (a) Each township hospital will establish an antibiotic stewardship working team including the township hospital director and a senior physician. The team will decide local antibiotic policies (b) The antibiotic stewardship team will hold peer-review meetings on antibiotic use monthly throughout the intervention period and embedded within the routine meetings of family physicians. Before each peer-review meeting, the antibiotic stewardship team will hold an internal meeting to prepare prescription reviews. The results will be sent to individual family physicians through WeChat. Each physician will see their performance of appropriate antibiotic prescribing against the hospital average (c) The antibiotic stewardship team will organise monthly peer-review meetings in township hospitals to ensure: (1) clear targets are set for appropriate use, (2) specific feedback is provided to high prescribers on improvement, (3) adjusting assessments for individual physicians based on their performance and (4) recording monthly meeting memos (d) The research team will make monthly supervisory visits to intervention township hospitals. The supervisory visits will ensure: (1) adherence to the interventional activities, (2) feedback and an opportunity to answer questions, (3) meeting with the antibiotic stewardship team to strengthen leadership and their commitment to reduce antibiotic prescriptions 2. Operational guidelines to reduce antibiotic prescribing for ARIs will be used. The guidelines will include patient symptom-based diagnostic algorithms, when to/ not to use antibiotics, and when narrow-spectrum antibiotics are preferred. Based on Chinese guidelines, chest x-ray examinations will be recommended when symptoms indicate pneumonia but clinical signs are not severe, or if a patient makes a second visit with signs indicative of pneumonia. Key health education messages during consultations with patients are also included (a) Every family physician in the township hospitals will receive an operational guideline both in printed and app-based form (b) Village doctors will receive a brief operational guide regarding appropriate use of antibiotics and referral 3. Systematic training including a half-day training workshop run by a county-level hospital senior physician and the research team will be given to family physicians and village doctors. This will involve: (a) Lectures, case discussions, role plays and Q&As on appropriate antibiotic prescribing practices for RTIs based on operational guidelines. Every family physician in the township hospitals will receive a training booklet both in printed and WeChat-app form (b) Using the WeChat app to monitor antibiotic use based on monthly reports from the EMR system to facilitate physicians’ discussions (c) Communication skills training when consulting with patients and/or caregivers 4. Improved electronic prescription system in the EMR to help township hospital family physicians make appropriate decisions when treating patients for RTIs, involving: (a) Embedded modules to encourage appropriate antibiotic prescribing practice, such as pops-up of laboratory test checklists and recommended antibiotics to prescribe when prescribing (b) An alarm system will be implemented to alert the family physician about any patient who re-visits any hospital within 14 days or who has been admitted within 1 month for a respiratory infection or sepsis after their index visit. In this scenario, chest x-ray and blood profile examinations will be recommended and recorded	1. Currently most township hospitals have an existing antibiotic stewardship programme. However, the programmes are often not functioning because of specific targets and activities are planned/implemented. Township family physicians do already hold monthly administrative meetings, but no time is spent on antibiotic prescribing peer-review discussions 2. Township hospital family physicians will prescribe antibiotics according to existing national guide on use of antibiotics which are not specifically designed for primary care facilities, and rarely used. Most physicians prescribe based on their group practice and existing knowledge/practices. Any messages given by control-arm family physicians will be at their own discretion based on their existing practice and training 3. Township hospital family physicians receive relevant medical training before they obtain their qualifications, but only a few of them have opportunities to receive continuing training afterwards and these trainings are usually not specifically for respiratory infections or antibiotics use. We will not provide any training to control-arm family physicians 4. Township hospitals already have a similar electronic prescription system in the EMR, but there is no clinical decision module, alarm system or pop-ups for recommended and non-recommended antibiotics. We will not make this available for control-arm hospitals

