#### Primary outcome

Our primary outcome is the proportion of prescriptions for eligible patients (aged 0–75 years with a diagnosed ARI, excluding pneumonia and other complications – see the ‘Eligibility criteria’ section) that contain one or more antibiotics, which (as per related literature) we refer to as the antibiotic prescription rate (APR). As in previous trials [17, 34] we will use the APR to measure the proportion of unnecessary antibiotic prescribing/use, given that most patients with URTIs and acute bronchitis do not benefit from antibiotics.

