#### Patient safety indicator

We will evaluate whether the intervention appears to increase adverse events; for example, because of antibiotics being withheld for appropriate conditions more frequently due to the intervention, by creating and evaluating an indicator of unintended harms. To do this we will use the EMR to track whether any patients subsequently become hospitalised in any hospital in the Shaoguan Prefecture, including its county- and prefectural-level teaching hospitals, due to respiratory infections or sepsis, within 30 days of their index visit to a participating township hospital during the trial period. This will allow us to calculate a cluster-level hospitalisation rate for trial participants as the number of hospitalisations for respiratory infections or sepsis per 100 outpatient consultations. We will compare both patient safety indicators between treatment arms.

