### Data collection and management

#### Clinical consultations and prescriptions

In township hospitals a prescription is required for each consultation to record the clinical visit to enable patients to receive reimbursements from the rural health insurance scheme. Therefore, although in theory patients may visit a family physician but not obtain a prescription this is rare in practice because patients do not feel that they are ‘being taken care of’ without receiving medication(s) [39]. Also, even when outpatient visit costs are not covered by the health insurance scheme patients still prefer to register their visits because the scheme covers much of their consultation costs [40].

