#### Primary and secondary outcomes

Following the baseline and the trial periods we will extract all eligible patient prescription data from the EMR for all township hospitals. The Prefecture Health Information Centre manages all EMR, and will provide encrypted and de-identified electronic prescription data (e.g. names, addresses and health insurance numbers will not be collected). We will then clean the data and enter it into a standard format database to store all outcome and covariate data (including diagnoses, medicines prescribed, medicine and consultation costs, plus patients’ age, sex, insurance status, date of visit, any related treatments, payment details and any re-visit or hospitalisation data). We will also collect relevant covariate data from all township hospitals, including family physicians’ age, sex, experience and qualification level, which we can be link to each prescription via unique prescriber IDs.

To allow us to exclude patient prescriptions from outcomes where the patients have excluding comorbidities, we will also record any comorbidities as per secondary diagnoses shown on prescriptions. We will also check medications listed on prescriptions to link them to possible diagnoses. For example, steroid inhalers with asthma or chronic obstructive pulmonary disease, anti-diabetic medications with diabetes, and anti-hypertensive medications with hypertension. The Prefecture Health Information Centre will use the encrypted personal health insurance numbers in each prescription to identify any long-term comorbidities recorded such as diabetes, hypertension, cardiovascular disease. We will also develop a list of keywords used locally in prescription diagnoses for respiratory infections (which are often symptom based), and will manually screen and code all prescriptions not containing an ICD-10 code of diagnosis.

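### The hospitalisation rate times its numerator from an undefined index visit but divides by consultations, so extra return visits in the intervention arm would dilute it

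*Protocol article*

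**What the plan says.** All of the following is in the protocol article.

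- **Outcomes:** the data are "EMR data on all prescriptions issued to eligible outpatients attending trial township hospitals" over the 12-month baseline and 12-month trial periods. No first-visit or episode restriction is stated.
- **Primary outcome:** "Our primary outcome is the proportion of prescriptions for eligible patients" that contain at least one antibiotic.
- **Clinical consultations and prescriptions:** "In township hospitals a prescription is required for each consultation". A return visit therefore creates a new prescription and a new consultation.
- **Patient safety indicator:** hospitalisations for respiratory infection or sepsis count if they occur "within 30 days of their index visit to a participating township hospital during the trial period". The rate is the "number of hospitalisations for respiratory infections or sepsis per 100 outpatient consultations". Neither this section nor the later data-collection section on patient safety says which visit is the index visit when a patient attends more than once.
- **Table 2:** the intervention arm alone gets an electronic alarm for a patient "who re-visits any hospital within 14 days".
- **Primary and secondary outcomes (data collection):** the database will hold "any re-visit or hospitalisation data", but no outcome definition uses the re-visit data.

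**The concern.** A rate should relate events to the units at risk of them. Here the numerator is tied to one visit per illness, while the denominator counts every visit. The intervention aims to change what happens at a visit, so it may also change whether the patient comes back. The denominator is then partly a result of treatment.

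This matters because the indicator exists to detect harm from withheld antibiotics. If patients sent home without an antibiotic return more often, their extra consultations lower the intervention-arm rate even when the risk of hospitalisation per illness is the same in both arms. The error runs towards reassurance, in the arm where harm is feared.

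The missing definition also leaves the start of the 30-day window open. If any visit may serve as the index visit, a patient who returns is followed for longer after falling ill than one who does not, so the numerator could shift as well.

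**Working it through.** The plan states no re-visit rate and no expected hospitalisation rate, so there is no figure of its own to reproduce here. The question is how far the denominator could move.

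**Inputs from the plan (Sample size):** APR at the first visit of an illness q = 0.80 in control; a 15-point reduction gives q = 0.65 in the intervention arm.

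**Assumptions:** at most one re-visit per illness; every re-visit is eligible and counted; re-visit probability u after no antibiotic and a after an antibiotic, the same in both arms; consultations are read as eligible ARI consultations.

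**Denominator.** Consultations per illness = 1 + r, where r = (1 − q)u + qa. With equal true risk per illness, the intervention-to-control ratio of rates per consultation is (1 + r_control)/(1 + r_intervention).

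| u | a | Control visits per illness | Intervention visits per illness | Denominator ratio | Spurious relative fall |
|---|---|---|---|---|---|
| 10% | 5% | 1.0600 | 1.0675 | 1.007 | 0.7% |
| 20% | 5% | 1.0800 | 1.1025 | 1.021 | 2.0% |
| 30% | 5% | 1.1000 | 1.1375 | 1.034 | 3.3% |
| 10% | 0% | 1.0200 | 1.0350 | 1.015 | 1.4% |
| 20% | 0% | 1.0400 | 1.0700 | 1.029 | 2.8% |
| 30% | 0% | 1.0600 | 1.1050 | 1.042 | 4.1% |
| 10% | 10% | 1.1000 | 1.1000 | 1.000 | none |

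Worked line for u = 20%, a = 5%: control r = 0.20 × 0.20 + 0.80 × 0.05 = 0.08; intervention r = 0.35 × 0.20 + 0.65 × 0.05 = 0.1025; 1.1025/1.08 = 1.021.

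The excess in the denominator ratio equals 0.15(u − a)/(1 + r_control). It vanishes when u = a and reverses if patients given antibiotics return more often.

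As an illustration, assume 1 hospitalisation per 100 illnesses in both arms. With u = 30% and a = 0, the reported rates are 1/1.06 = 0.943 and 1/1.105 = 0.905 per 100 consultations. At u = 50%, outside the main range, they are 0.909 and 0.851, a fall of about 6%.

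**APR under the same model.** Let s be the probability of an antibiotic at a re-visit. Per-prescription APR = (q + sr)/(1 + r). The share of illnesses ever given an antibiotic = q + (1 − q)us. The fall at the index visit is 15.0 points throughout.

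| u | a | s | Per-prescription fall | Ever-treated fall |
|---|---|---|---|---|
| 20% | 5% | 0.8 | 80.0 − 66.4 = 13.6 | 83.2 − 70.6 = 12.6 |
| 10% | 10% | 0.8 | 80.0 − 66.4 = 13.6 | 81.6 − 67.8 = 13.8 |
| 30% | 0% | 0 | 75.5 − 58.8 = 16.6 (unrounded inputs) | 80.0 − 65.0 = 15.0 |

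The per-prescription fall lies above or below either comparator, depending on who returns and what they are given.

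**The case against.** **The effect on the safety rate is small and conditional.** The protocol does not say that withholding antibiotics brings patients back; the 14-day alarm is a safety feature, not a forecast. Not every return enters the denominator either: returns diagnosed as pneumonia are ineligible, and returns to hospitals outside the trial are not counted, so the model probably overstates the growth. All of this stands, and it is why the size is given as a range under assumptions.

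**Blinded reviewers adjudicate the hospitalisation charts.** They do, and only admissions attributed to withheld or otherwise inappropriate antibiotics count towards the adverse-event outcome. That cleans the numerator. It does nothing for a denominator made of consultations.

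**The definition may be in the full analysis plan.** The operational detail of an index visit may well be there. The consultation denominator, however, is fixed in the published outcome definition.

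**A stronger reading is tempting:** that counting repeat visits makes the trial overstate the fall in APR, because an antibiotic given late is partly scored as one avoided. The documents do not support this. It needs re-visit rates that the protocol does not give. Against illnesses ever treated, the sign reverses when re-visits are unrelated to antibiotic receipt (13.6 against 13.8 points). Against the index visit, the same assumptions that suggest overstatement give an understatement (13.6 against 15.0). Per-prescription APR is also a legitimate measure of prescribing behaviour, which is what the intervention targets.

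**Conclusion.** The point holds for the safety indicator. Its numerator and denominator use different units, the index visit is undefined, and the intervention can move the denominator. If withheld antibiotics raise eligible return visits, the intervention-arm rate is diluted by about 1–4% in relative terms. That rests on assumed re-visit rates of 10–30% after no antibiotic and 0–5% after one, on the planned 80% against 65% APR, and on every return being counted. With no difference in return visits there is no dilution.

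The distortion is modest, and nothing here shows that it would change a conclusion. It is worth removing because it leans towards reassurance on a measure meant to detect harm. For the APR, the direction cannot be determined from the protocol, and the primary outcome need not change.

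**What to change.** 1. Define an index visit identically in both arms: for example, an eligible ARI visit with no ARI visit by the same linked patient in the previous 14 days. The trial team should set the window. Start the 30-day period at that visit and assign each hospitalisation to one index visit only.
2. Use index visits as the denominator of both the hospitalisation rate and the adverse-event rate.
3. Report re-visit rates by arm, so that readers can see whether the visit count depended on treatment.
4. Keep per-prescription APR as the primary outcome. Add one pre-specified sensitivity analysis giving APR at the index visit and the proportion of episodes with any antibiotic.

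**Cost:** mostly definition and programming, since re-visit data are already to be collected. The research team will not receive insurance numbers, so the Prefecture Health Information Centre, which already links visits to admissions by encrypted number, must also supply the visit-to-visit linkage. Visits without a usable number cannot be linked; their count by arm should be reported.

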#### Primary outcome

Our primary outcome is the proportion of prescriptions for eligible patients (aged 0–75 years with a diagnosed ARI, excluding pneumonia and other complications – see the ‘Eligibility criteria’ section) that contain one or more antibiotics, which (as per related literature) we refer to as the antibiotic prescription rate (APR). As in previous trials [17, 34] we will use the APR to measure the proportion of unnecessary antibiotic prescribing/use, given that most patients with URTIs and acute bronchitis do not benefit from antibiotics.

#### Secondary outcomes

We will also collect and create the following set of secondary outcomes, which will allow us to evaluate whether the intervention affects the proportion of antibiotic-containing prescriptions where the antibiotic(s) are of a specific class or method of delivery. The following set of indicators is based only on those eligible prescriptions containing at least one antibiotic: (1) the broad-spectrum antibiotic prescription rate: the proportion that contain one or more broad-spectrum antibiotics (we define broad-spectrum antibiotics as those antibiotics that act on the two major bacterial groups gram-positive and gram-negative, or any antibiotic that acts against a wide range of disease-causing bacteria); (2) the fluoroquinolone prescription rate: the proportion that contain one or more fluoroquinolone antibiotics; (3) the multiple antibiotic prescription rate: the proportion that contain two or more antibiotics of any kind; (4) the intravenously injected antibiotic prescription rate: the proportion that contain any antibiotics delivered by intravenous injection. As the intervention will address appropriate use of antibiotics for bacterial ARIs, we will also measure, taking the total number of antibiotics prescribed per township hospital as the denominator and (5) the proportion that contain any antibiotics in the *Access* group of the *WHO’s 2019 Essential Medicines List* classification [35]. As all these outcomes have denominators that only include eligible prescriptions containing one or more antibiotics, when analysed they will effectively be creating ‘outcome-based subgroups’ that are defined post randomisation [36]. This is a common, but often unrecognised, issue that can introduce bias into the treatment-effect estimates for such outcomes. However, there are no clearly applicable/feasible solutions for our situation [36], and so we will treat the results for these specific outcomes as exploratory.

We will also collect and create the following secondary outcomes based on all eligible prescriptions. In our previous trial, we observed an increased use of Traditional Chinese Medicines, likely as alternatives to antibiotics, and a widespread misuse of glucocorticoids [17]. Thus, we will also measure: (6) the proportion containing any Traditional Chinese Medicines and (7) the proportion containing any glucocorticoids. Lastly, to evaluate if and how the intervention affects the mean cost of prescriptions issued to eligible patients we will also measure: (8) the average cost of a prescription, based on the cost of any medicines and (9) the average cost of a consultation (one per prescription), based on all costs including medicines, tests and the consultation.

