### Sample size

Our sample size is calculated based on our primary APR outcome. Previous exploratory work suggested the existing township hospital APR level to be around 80%. We assume that the treatment will reduce the intervention arm APR by more than 15 percentage points during the trial period, based on how effective the previous related trial was [25], which is viewed as the minimum clinically important effect in the context of the extremely high existing APR levels. Based on our previous trial [25] we assume that the intra-cluster correlation coefficient will be 0.14 in the intervention arm and 0.09 in the control arm here, and based on our exploratory work we assume that we will be able to collect at least 500 eligible prescriptions per township hospital during the trial period, which we assume as our fixed cluster size. Based on these assumptions we estimated that we will require 17 clusters per arm to detect a 15-percentage-point or greater absolute reduction in the APR with 80% power using a two-sided hypothesis test with an alpha of 0.05 [37]. Because our previous trial data indicated potentially important county-level differences in baseline and during-trial-period APR levels and in the magnitude of the treatment effect, we also plan to stratify our randomisation by county. Therefore, this sample size also accounted for an unequal allocation ratio within strata, and, specifically given the number of clusters available in each county, it accounted for a within-county intervention-to-control allocation ratio of 8:9, which we chose in favour of the control arm for logistical purposes.

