### Statistical analyses

We will report all results according to the ‘Consolidated Standards of Reporting Trials: Extension for Cluster Trials’ (CONSORT) guidelines [41]. Prior to the end of the trial and before the trial dataset is created we will produce a full statistical analysis plan pre-specifying and detailing all planned analyses. In summary though, in our main results paper we will present appropriate descriptive statistics for all relevant patient, family physician, township hospital and village clinic characteristics, along with appropriate summary statistics and their associated 95% confidence intervals for all outcomes by treatment arm at baseline and during the trial. Then for all outcomes we will produce a main set of estimates of treatment effectiveness using cluster-level methods of analysis suitable for cluster trials. This set of estimates will be used as the primary evidence for determining how effective the treatment appears to be for the primary and all secondary outcomes. There will no interim analyses.

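### Secondary outcomes 1 to 4 need versions over all eligible prescriptions, because antibiotic-only denominators can mislead in sign; outcome 5 needs a single unit

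*Protocol article*

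**What the plan says.** All references are to the protocol article.

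- **Secondary outcomes, items 1 to 4** (broad-spectrum, fluoroquinolone, multiple and intravenous antibiotics): "The following set of indicators is based only on those eligible prescriptions containing at least one antibiotic".
- **Secondary outcomes, item 5** (WHO Access group) is introduced by "taking the total number of antibiotics prescribed per township hospital as the denominator" but is then worded as a proportion of items containing an Access antibiotic. The sentence after it describes the denominators of all five outcomes as eligible prescriptions with at least one antibiotic.
- **Recognition of the problem:** the same section says of these outcomes that "they will effectively be creating ‘outcome-based subgroups’ that are defined post randomisation", and that this can bias treatment effects. It then states that "there are no clearly applicable/feasible solutions for our situation [36], and so we will treat the results for these specific outcomes as exploratory".
- **Secondary outcomes, items 6 to 9** use the full denominator: "We will also collect and create the following secondary outcomes based on all eligible prescriptions". Items 6 and 7 are proportions.
- **Outcomes**, on the data: "We will collect all outcomes and variables from EMR data on all prescriptions issued to eligible outpatients attending trial township hospitals".
- **Sample size** puts the existing APR at about 80% and assumes a reduction of 15 points or more.
- **Statistical analyses** applies the Holm method to the secondary outcomes and makes no exception for items 1 to 5.

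**The concern.** The event that admits a prescription to the denominator of outcomes 1 to 5 is the primary outcome itself. The intervention is built to change it, and to change it selectively. The Intervention section teaches that antibiotics are inappropriate for most upper respiratory infections, and that first-line agents are appropriate for certain bacterial infections and bronchitis. If the training works, the prescriptions that still contain an antibiotic will have a different case mix in the two arms. The variables listed under Data collection and management include diagnosis, age and sex but no direct measure of severity, so covariate adjustment may not remove the difference.

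What is at stake is how the class-specific results are read. A programme that lowers fluoroquinolone or intravenous use per consultation could appear to raise it. A comparison without this problem is within reach, and the protocol's stated reason for not offering one does not hold against its own outcomes 6 and 7.

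**Working it through.** **1. The plan's own figure.** The protocol gives no figure for outcomes 1 to 5. Its 17 clusters per arm concern the APR, and they reproduce. With p0 = 0.80, p1 = 0.65, m = 500 and ICCs of 0.09 (control) and 0.14 (intervention):

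- control variance = 0.80 × 0.20 × (1 + 499 × 0.09)/500 = 0.01469
- intervention variance = 0.65 × 0.35 × (1 + 499 × 0.14)/500 = 0.03224
- clusters per arm = (1.96 + 0.84)² × (0.01469 + 0.03224)/0.15² = 16.4, rounded up to 17

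Nothing below changes this.

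**2. Change in the denominator.** Per 500 eligible prescriptions, the antibiotic-only denominator is 500 × 0.80 = 400 in control and 500 × 0.65 = 325 in intervention. That is a fall of 75/400 = 18.75%.

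**3. Sign reversal in a two-stratum illustration.** The strata and class shares are assumptions; the documents give none. Half the cases are mild and half severe. Fluoroquinolones make up 10% of antibiotic prescriptions in mild cases and 30% in severe cases, in both arms.

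| | Control | Intervention |
|---|---|---|
| Antibiotic given, mild | 70% | 45% |
| Antibiotic given, severe | 90% | 85% |
| APR | 80% | 65% |
| Fluoroquinolone per eligible prescription | 0.5×0.70×0.10 + 0.5×0.90×0.30 = 17.0% | 0.5×0.45×0.10 + 0.5×0.85×0.30 = 15.0% |
| Fluoroquinolone per antibiotic prescription | 0.170/0.80 = 21.3% | 0.150/0.65 = 23.1% |

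The conditional rate rises by 1.8 points while actual use falls by 2.0 points.

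**4. General condition.** Let s be the class share among control antibiotic prescriptions, and let x be the part of the 15 removed points that belongs to the class. No retained prescription changes class. The conditional difference is (0.80s − x)/0.65 − s, which is positive whenever x < 0.15s. So for any x between 0 and 0.15s, use falls but the conditional rate rises. At s = 0.5 and x = 0.04, use falls from 40 to 36 per 100 eligible prescriptions, while the conditional share rises from 50.0% to 36/65 = 55.4%.

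**5. Range.** Setting x = 0.15 and x = 0 gives the extremes of the conditional difference from selection alone:

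| Assumed s | Lowest | Highest |
|---|---|---|
| 0.2 | −18.5 points | +4.6 points |
| 0.3 | −16.2 | +6.9 |
| 0.5 | −11.5 | +11.5 |
| 0.7 | −6.9 | +16.2 |
| 0.8 | −4.6 | +18.5 |

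**6. Holm family.** With nine secondary outcomes the first-step threshold is 0.05/9 = 0.0056. For outcomes 6 to 9 alone it would be 0.05/4 = 0.0125. As written, five of the nine places go to outcomes that the protocol itself calls biased and exploratory.

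**7. Outcome 5.** A prescription with one Access and one non-Access antibiotic scores 1 of 1 if prescriptions are counted and 1 of 2 if antibiotics are counted. The two readings define different outcomes.

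**The case against.** The strongest reply is that the all-eligible rate answers a different question. It equals the APR times the class share, so it falls when the APR falls even if no prescriber changes class. With an unchanged share of 20% it goes from 0.80 × 0.20 = 16.0% to 0.65 × 0.20 = 13.0%; with an unchanged share of 80% it goes from 64.0% to 52.0%. The stated aim of outcomes 1 to 5 is class choice among antibiotic prescriptions, and the all-eligible rate does not identify that. This stands. It argues for adding the all-eligible versions and reading them beside the APR, and against simply replacing the conditional ones.

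The protocol also discloses the bias and labels the outcomes exploratory, which stands too. Several stronger readings go beyond the text:

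- **That the protocol denies any solution exists.** Its wording is softer: none that is clearly applicable or feasible in its situation.
- **That the outcomes are uninterpretable.** They remain usable as descriptions of what was prescribed in each arm.
- **That their status is contradicted in Statistical analyses.** A reader might infer this from "This set of estimates will be used as the primary evidence for determining how effective the treatment appears to be". In context that sentence ranks the main set of estimates above the sensitivity sets, not one outcome above another. Using Holm on exploratory outcomes is not a contradiction either, though it does charge the other secondary outcomes for them.
- **That outcome 5 takes in antibiotics for other illnesses.** The Outcomes section limits all outcomes to prescriptions of eligible outpatients.

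**Conclusion.** The point holds as one of missing comparisons and definitions. Outcomes 1 to 5 condition on an event that the trial is designed to change by at least 15 points. The protocol's statement on solutions overlooks versions of outcomes 1 to 4 that need no new data, fit the same two-stage analysis, and are as well protected by randomisation as the primary outcome. The conditional results can mislead in sign: 21.3% to 23.1% against 17.0% to 15.0% in the illustration. Across assumed class shares of 20% to 80%, selection alone could move them by anything from −18.5 to +18.5 points.

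These sizes use the planned APRs of 80% and 65% together with class shares and strata that are assumed. They show that reversal is possible, not that it is likely. Outcome 5 is inconsistent in its unit as written. The primary outcome, outcomes 6 to 9 as defined, and the sample size are unaffected.

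**What to change.** 1. Add, as the inferential comparisons, the proportions of all eligible prescriptions containing a broad-spectrum antibiotic, a fluoroquinolone, two or more antibiotics, and an intravenous antibiotic. State that they are to be read beside the APR and do not isolate class choice among those treated.
2. Keep the conditional versions as descriptive or exploratory, and say under Statistical analyses that they are outside the Holm family.
3. Define outcome 5 in one unit, for example Access-group antibiotics divided by all antibiotics on eligible prescriptions, reported descriptively. Add the proportion of all eligible prescriptions containing a non-Access antibiotic as its randomised counterpart.
4. Replace the sentence on the absence of solutions with one saying that the all-eligible versions give the randomised comparison and the conditional ones do not.

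The cost is a few extra outcomes and a different estimand for the class-specific comparisons. If all five new comparisons enter the Holm family with outcomes 6 to 9, it again has 5 + 4 = 9 members, so the first-step threshold stays at 0.0056, now spent on randomised comparisons. No new data are needed. The protocol says the analysis plan will be completed before the trial dataset is created, so that is a natural place for the change.
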